***Secondary Measures***	
Parent-child interaction	
Parental knowledge/attitudes about childhood obesity	
Acceptability of the intervention to mothers and families	
Partner and family support	

^1 ^'Extra' foods include chips, wedges & crisps; takeaway burgers, pizza & chicken; sweetened drinks

In addition, two validation studies of measures of physical activity and nutrition for children aged 2–4 years are currently underway. These studies are being led by the NSW Centre for Public Health Nutrition, and the Discipline of Paediatrics & Child Health at the University of Sydney. The measurement tools will allow us to make detailed assessments of dietary intake and levels of physical activity and sedentary behaviour in order to detect the impact of the intervention.

Standard demographic and socio-economic information, and secondary measures will also be collected using questions from the NSW Child Health Survey 2001 [38].

Measurement points for both control and intervention groups for Phase One of the study will occur in participants' homes at baseline, 12 and 24 months. Phase Two measurements will take place at 3, 4 and 5 years.

Nurses trained in anthropometric techniques will collect measurements of height, weight and waist size in children at 2, 3, 4 and 5 years using stadiometers, scales and tape measures.

### Phase two study

Additional funding will be sought for a further follow-up of the cohort to assess the outcomes indicated above at 3, 4 and 5 years of age. This is an important dimension of the project, which will strengthen the overall study in the following ways. First, longer-term follow up will allow an assessment of whether any behavioural changes resulting from the intervention are sustained over time. Second, nutritional and physical activity behaviours in the first two years of life may not have a significant bearing on weight status during this immediate period. Finally, longer-term follow-up of the control group will permit prospective, observational analysis of the prevalence and determinants of overweight and obesity within a large, population-based sample during the early years.

### Data analysis

BMI will be calculated as weight (kg)/height (metres) squared and children at two to five years of age will be classified as not overweight or obese, overweight or obese, based on the International Obesity Taskforce recommended age-standardised BMI cut points [43].

The outcomes will be compared between the intervention and control groups. For continuous variables, such as knowledge and attitudes scales and BMI, means will be compared using t-tests, or non-parametric equivalents for non-normally distributed variables. For categorical variables, chi-squared tests will be used. All analyses will be by intention to treat.

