### Participants and recruitment

All pregnant women who attend antenatal clinics of Liverpool and Campbelltown Hospitals will be approached by research nurses with a letter of invitation and information about the study. These two hospitals have been chosen since they attract a large number of patients from the areas of South West Sydney with the relatively high levels of disadvantage based on Social Economic Indexes For Areas (SEIFA) rankings [30] and a broad ethnic mix. Once eligibility is established and consent obtained, women will be asked to fill in a registration form with their contact information to allow the nurses to make further arrangement for the baseline data collection and random allocation to study condition. Mothers will only be entered into the study after written consent is obtained and eligibility criteria are met.

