### Registration and randomisation

Information collected from the registration form will be entered into a password-protected Microsoft Access database. A letter will be sent by the research nurse to inform the hospital obstetrician that the mother is enrolled in this research trial. An appointment for the first home visit will be made with all participating mothers by a letter, followed by a telephone call. The first home visit will take place between weeks 30 to 36 of pregnancy.

Random allocation to either the intervention or control group is concealed by sequentially numbered, sealed opaque envelopes containing the group allocation, which will be determined by a computer generated random number. Randomisation will be stratified by hospital, with a block size of 50. A research assistant who has no direct contact with participating mothers will be responsible for generating the random numbers and preparing the envelopes.

During the first home visit, immediately after the baseline data collection, the nurse will open the sealed envelope and inform the mother of the outcome of randomisation.

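### The stated tests ignore the hospital strata used in randomisation and any usable baseline values: valid, but slightly conservative and less precise than the design allows

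*Protocol article*

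**What the plan says.** The Data analysis section of the protocol article names the tests. For continuous outcomes such as BMI and attitude scales, "means will be compared using t-tests, or non-parametric equivalents for non-normally distributed variables". Otherwise, "For categorical variables, chi-squared tests will be used". It closes with "All analyses will be by intention to treat". No section mentions a stratified test, a regression model, or adjustment for hospital or any other covariate.

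The design is described elsewhere:

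- Registration and randomisation: "Randomisation will be stratified by hospital, with a block size of 50".
- Participants and recruitment gives two hospitals, hence two strata: "All pregnant women who attend antenatal clinics of Liverpool and Campbelltown Hospitals will be approached".
- Registration and randomisation places baseline before allocation: "During the first home visit, immediately after the baseline data collection, the nurse will open the sealed envelope". It also dates that visit: "The first home visit will take place between weeks 30 to 36 of pregnancy".
- Outcome measures lists the Phase One measurement points, in participants' "homes at baseline, 12 and 24 months".

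**The concern.** Stratifying by hospital makes the arms nearly equal within each hospital, so differences between hospitals contribute almost nothing to the true variance of the treatment comparison. A plain two-sample test still counts that between-hospital variation in its standard error. The standard error is then too large for the design, intervals are a little too wide, and the test rejects less often than its nominal level.

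Separately, where an outcome can be measured in the mother or family at the antenatal visit, comparing follow-up means alone discards information already collected. At stake is precision. The treatment estimate is not biased and the false-positive rate is not inflated.

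**Working it through.** **1. The article's own figure.** Sample size, calculation 1, gives 252 per group for a BMI z-score difference of 0.25. With a z-score SD of 1 (assumed; not stated), two-sided 5% and 80% power (stated only with calculation 2):

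n = 2 × (1.96 + 0.8416)² / 0.25² = 2 × 7.849 / 0.0625 = 251.2, so 252 per group. It reproduces, and it does not rely on adjustment.

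**2. Ignoring hospital, continuous outcome.** The article gives no hospital difference, so a range is used. Let D be the gap between hospital means in within-hospital SDs, with two equal-sized hospitals and arms balanced within each. Between-hospital variance is D²/4 against a within-hospital variance of 1, so the unadjusted standard error is too large by a factor √(1 + D²/4). Unequal hospitals, with share p in one, give p(1−p)D², which is smaller, so equal sizes are the least favourable case.

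- Actual size of the unadjusted test: 2 × [1 − Φ(1.96 × √(1 + D²/4))].
- Power at 252 per group and 0.25 SD: nominal standard error s = √(2/252) = 0.0891; true standard error t = s / √(1 + D²/4). Unadjusted power is Φ((0.25 − 1.96s)/t); adjusted power is Φ(0.25/t − 1.96).

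| D | SE too large by | Actual size | Power, unadjusted | Power, adjusted | Loss (points) |
|---|---|---|---|---|---|
| 0 | 0% | 5.0% | 80.13% | 80.13% | 0 |
| 0.2 | 0.5% | 4.9% | 80.25% | 80.52% | 0.3 |
| 0.3 | 1.1% | 4.75% | 80.39% | 80.99% | 0.6 |
| 0.5 | 3.1% | 4.3% | 80.85% | 82.45% | 1.6 |

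**3. Ignoring hospital, binary outcome.** The same argument uses the ratio of average within-hospital variance to total variance. For assumed hospital rates of 20/30%, 15/35% and 10/40%, the ratios are 0.987, 0.947 and 0.880. For 10/40%: [(0.1 × 0.9 + 0.4 × 0.6)/2] / (0.25 × 0.75) = 0.165/0.1875 = 0.880. The nominal 5% chi-squared test then runs at about 4.9%, 4.4% and 3.7%.

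**4. Which outcomes can have a baseline value.** Baseline falls at 30 to 36 weeks of pregnancy, and child anthropometry starts at age 2 (Outcome measures). So breastfeeding, solids, child diet, serving size, television viewing, active play and child BMI have none. Of the listed measures, family nutrition and physical activity (primary) and parental knowledge and attitudes (secondary) could. The article does not list the baseline instruments, so this is what could be measured, not what is confirmed.

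**5. Gain for those outcomes.** With baseline-to-follow-up correlation r (assumed), residual variance falls by the factor 1 − r². Power = Φ(0.25 / (0.0891 × √(1 − r²)) − 1.96).

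| r | Power at 252 per group | n per group for the same power |
|---|---|---|
| 0 | 80.1% | 252 |
| 0.3 | 83.7% | 252 × 0.91 = 229.3, so 230 |
| 0.5 | 90.0% | 252 × 0.75 = 189 |

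The 252 and 0.25 come from the BMI calculation. Here they stand for a maternal or family outcome with the same standardised effect. At 313 per arm, the number planned after drop-out, power for 0.25 SD is about 88% unadjusted and 91% or 95% at these correlations.

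**The case against.** The strongest reply is that unadjusted tests are valid after stratified randomisation. The error is on the safe side, there are only two strata, and both hospitals were chosen because they draw on disadvantaged parts of South West Sydney, so their means may differ little. All of that stands, and it limits the point to efficiency. An analysis plan that is not shown may also add adjusted analyses. But the article does not leave the test open: it names the tests, and they do not match the randomisation it describes.

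A reader might infer more in four ways, none of which the document supports:

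- *That baseline adjustment would greatly increase power for the main child outcomes.* They have no baseline value. Maternal or socio-economic covariates might help them a little, but the article gives nothing from which to size that.
- *That the trial risks false-positive findings.* The direction is the opposite.
- *That participants lost to follow-up will simply be dropped, and that imputation from the 12-month visit would repair this.* The article is silent on missing data, a detail it may leave to the full plan. Child anthropometry is not listed at 12 months, so there would be no earlier BMI to impute from.
- *That allowing rank tests lets the results choose the test.* The wording is conventional shorthand and does not say that the choice follows a look at results by arm. It is a minor matter, which a regression analysis would largely remove.

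One technical caution also stands. Logistic regression with hospital estimates a conditional odds ratio, which is not the same quantity as the difference in proportions used in calculation 2 of the sample size.

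**Conclusion.** The point holds as a modest efficiency point. The named analysis does not use the stratification factor, and it forgoes baseline values for the few outcomes that could have them. For hospital gaps of 0.2 to 0.5 SD, the cost is an actual test size of about 4.9% to 4.3% and a power loss of about 0.3 to 1.6 points. For maternal, family and knowledge or attitude outcomes only, adjustment would lift power from 80% to about 84% (r = 0.3) or 90% (r = 0.5). These sizes rest on assumed hospital gaps and correlations, a z-score SD of 1, equal-sized hospitals, and 252 per group with a 0.25 SD effect. The planned conclusions would not be invalid if nothing changed.

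**What to change.** In Data analysis, replace the two-sample tests as the main comparison:

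- Continuous outcomes: linear regression on treatment arm and hospital.
- Binary outcomes: a Mantel-Haenszel analysis stratified by hospital, or logistic regression including hospital. A Mantel-Haenszel risk difference keeps the scale used in the sample size; if logistic regression is chosen, also report the difference in proportions.
- Add the baseline value of the outcome only where it is collected at the antenatal visit (maternal and family nutrition and activity, knowledge and attitudes), and list those outcomes by name.
- Report each difference with a 95% interval.

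If a separate analysis plan already does this, aligning the article's wording with it is enough. The cost is a few sentences and a little more programming. No new data, visits or participants are needed, and the stated sample size can stand.

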## Discussion

Efforts to tackle childhood obesity must begin in early life. The epidemic is evident in children as young as two years of age. Attempts to treat existing obesity have had limited success. This may be due to the fact that established patterns of eating and physical activity behaviour are difficult to modify. Early life nutrition and physical activity levels are positively associated with obesity in childhood and later life. Moreover, parents with new-born children are very receptive to advice and support about lifestyle changes for the whole family from an early childhood health professional.

Few systemic interventions aimed at preventing early childhood overweight and obesity have been implemented and evaluated. This study will generate new evidence in the important area of childhood overweight and obesity prevention through a family based early intervention program. If successful, this study will also result in the development of a model of "best practice" for promoting healthy feeding and physical activity in infants under two years of age, which could be used nationally and internationally.
